## Abstract

**Background:**

Road trauma is a leading cause of death and disability for young Australians (15–24 years). Young adults are overrepresented in crashes due to sleepiness, with two-thirds of their fatal crashes attributed to sleepy driving. This trial aims to examine the effectiveness of a sleep extension and education program for improved road safety in young adults.

**Methods:**

Young adults aged 18–24 years (n = 210) will be recruited for a pragmatic randomised controlled trial employing a placebo-controlled, parallel-groups design. The intervention group will undergo sleep extension and receive education on sleep, whereas the placebo control group will be provided with information about diet and nutrition. The primary outcomes of habitual sleep and on-road driving performance will be assessed via actigraphy and in-vehicle accelerometery. A range of secondary outcomes including driving behaviours (driving simulator), sleep (diaries and questionnaire) and socio-emotional measures will be assessed.

**Discussion:**

Sleep is a modifiable factor that may reduce the risk of sleepiness-related crashes. Modifying sleep behaviour could potentially help to reduce the risk of young driver sleepiness-related crashes. This randomised control trial will objectively assess the efficacy of implementing sleep behaviour manipulation and education on reducing crash risk in young adult drivers.

## Introduction

1

Globally, more deaths of young adults (aged 15–24 years) are caused by road crashes than are caused by disease, drug use, suicide, violence, and war [1]. In Australia, young adults constitute approximately 12% of the population [2], and account for nearly 19% of all crash-related fatalities [3]. While the causes of road crashes are multifactorial, sleepiness is a leading determinant, contributing to 20–30% of all motor vehicle crashes globally [[4], [5], [6]]. Young adults are over-represented in sleepiness-related crashes, accounting for over two-thirds of all crashes [[7], [8], [9]]. Crashes attributed to sleepiness are typically more severe or fatal than are other types of crash because drowsiness, or even sleep onset (e.g., microsleeps), prevents drivers from braking or attempting any correction before the collision [10]. Current road safety strategies fail to adequately address the contribution of sleep loss to road deaths.

Young adults frequently drive when they are sleepy, which increases their crash risk. In one study, more than 23% of all young adults drove when they ‘were close to falling asleep’ [11], with 1 in 4 reporting a near-crash or crash in the past year due to sleepiness [12]. A range of lifestyle factors unique to this developmental period, including educational demands combined with part-time employment, and increased socializing at night are some of the most common drivers contributing to lost sleep and fatigued driving in this group [13].

Sleepiness-related crashes occur primarily due to inadequate sleep [10,[14], [15], [16], [17]] and young adults are chronically sleep deprived. The 2016 American Academy of Sleep Medicine (AASM) [18], recommends 7–9 h s of sleep for most 18–25-year-olds. Despite this, up to 60% of young adults (17–24 years) rate themselves as poor sleepers, 25% report getting less than 6.5 h s of sleep each night, and 20% report not sleeping at all at least one night in the past month [19]. The cognitive deficits associated with chronic daily sleep loss are cumulative and dose-dependent [20], which means that young adults who obtain 30 min less sleep per night than the recommended amount can find themselves with a 3½ hr sleep debt by the end of the week [[21], [22], [23], [24]]. Sleeping between 6 and 7 h in a 24-h period can *double* an individual's risk of a road crash, and sleep being restricted to less than 6 h per night nearly quadruples the risk [16,17]. Young adults may also be uniquely vulnerable to the detriments of sleep loss, since the brain areas responsible for complex higher order cognitions including decision making, set-shifting and risk and reward perception are still developing [25]. Despite the over representation of young adults in road crash fatalities, current road safety strategies such as education, detection and enforcement have failed to directly target driver sleepiness as a cause of young driver fatalities.

It is possible that an intervention targeted at increasing young drivers' habitual sleep duration (i.e. sleep *extension*) may result in reduced sleepiness and reduced associated crash risk for young drivers, and a reduction in secondary risk-related behaviours. Sleep extension involves increasing *habitual sleep duration* to reduce the accumulation of sleep debt by increasing opportunities for sleep (i.e. prescribing increased ‘time in bed’ by advancing bed-time), improving behavioural factors that promote sleep (e.g. regularity of bedtimes/wake-up times), and reducing stimulants impairing sleep (e.g. caffeine, evening artificial light exposure, digital device use etc.). Controlled experimental studies have demonstrated the benefits of increasing sleep duration on resilience to future fatigue, and improved attention [[26], [27], [28]], both key protective factors in road crashes [29,30]. Recent evidence from ‘at-home’ sleep extension intervention studies (with 'prescribed’ additional time in bed at home, as opposed to the controlled laboratory setting) suggest that sleep prescription may extend sleep duration by up to 60 min [31,32], 90 min [[33], [34], [35]], or by up to 20% of the participants' habitual sleep duration per evening [36]. Likewise, gradual sleep extension in adolescents' home environment can result in increased sleep duration and time in bed, improved cognitive performance and divided attention [37]. These data suggest increasing time in bed may increase sleep duration in the home environment. The results of such an increase and subsequent effects on behaviours such as driving have not yet been determined. As such, we propose a pragmatic randomised controlled trial of an intervention targeted at young sleepy drivers to increase habitual sleep duration to improve resilience to sleepiness and reduce their on-road crash risk.

### Methods/design

1.1

#### Trial objectives

1.1.1

The primary trial objective is to test the effectiveness of a sleep extension and education intervention on objective indices of sleep and risky driving performance of chronically sleep-deprived young adults (18–24 years old).

The secondary objective of the trial is to assess the effects of the sleep extension and education intervention on daily subjective indices of sleep, and other risk factors for adverse driving outcomes (e.g., higher order cognitive functions, alcohol use, stress, and mood).

We hypothesise that, in comparison to the placebo control group, the intervention group will;(1)increase their habitual sleep duration by at least a clinically meaningful 25 min per night on average,(2)decrease their frequency of acute sleep loss episodes (<6 h s of sleep) across a typical week,(3)demonstrate reductions in high risk driving performance on the road and in the driving simulator.(4)improved performance on computerised executive-function tasks associated with behavioural self-regulation.

#### Sample size

1.1.2

A minimum sample size of 189 participants was initially calculated. We will aim to recruit 210 participants, allowing for ∼10% attrition at follow-up (consistent with drop-out from our previous studies in this age cohort). Based on the authors’ previous studies using the same measurement approach (h^2^_p_ = 0.12–0.37) [38], this sample size will provide 90% power, with a significance level of *p* = 0.05, to detect a 'small’ change in the primary driving outcome based on a parallel groups design with 0.3 correlation among the repeated measures. In addition, this sample size will provide 90% power to detect a 'small-medium effect size’ of a 5% increase in mean objective sleep duration (primary sleep outcome - equivalent to approximately 25 min additional sleep per night). This is a clinically and physiologically significant change [39], representing almost three extra hours of sleep each week. Based on our previous laboratory work [38] the study is also sufficiently powered for all proposed secondary outcomes.

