##### Randomisation and blinding

1.1.3.1

Following successful completion of screening and informed consent procedures, participants will be randomly allocated to either the Sleep Intervention group or the Nutrition ‘Placebo’ group by a data manager blind to participant recruitment using a computer-generated randomisation schedule. Participants will not be informed of their group allocation before completion of their baseline laboratory assessments to ensure a stable and equal baseline across participants.

The nature of the intervention does not permit fully blinding participants to their allocation status. Therefore, the trial will be partially blinded to prevent performance and attrition biases. However, the study aims and outcomes will be concealed, and the initial recruitment premise will be '*a study of health, activity, and transport’* to reduce expectancies. Additionally, evaluation of the outcomes will be conducted by staff blinded to participant allocation (e.g., an independent statistician), and the use of objective outcome measures will minimise the risk of ascertainment bias. A full explanation of both the real aims of the research and reasons for the concealment will subsequently be made available to participants upon completion of their participation or upon withdrawal from the study.

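### The claimed 90% power for a 'small' driving effect does not reproduce for the design described; 189 completers give 90% power at about 0.45 to 0.56 SD on the primary contrast

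*Protocol article*

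**What the plan says.** All in the protocol article.

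- Sample size (1.1.2): "A minimum sample size of 189 participants was initially calculated", and "We will aim to recruit 210 participants", to allow for about 10% attrition.
- The same section says that "this sample size will provide 90% power", "with a significance level of *p* = 0.05", for a small "change in the primary driving outcome based on a parallel groups design with 0.3 correlation among the repeated measures". It states no numeric effect, SD, test or sidedness. The basis offered is the authors' earlier work, with partial eta squared of 0.12 to 0.37. The sleep outcome is described separately, as small-medium.
- The section closes by saying, from the same laboratory work, that "the study is also sufficiently powered for all proposed secondary outcomes".
- Randomisation and blinding (1.1.3.1): "participants will be randomly allocated to either the Sleep Intervention group or the Nutrition" placebo group. No allocation ratio is given.
- Primary outcome 1 (2.2): the primary analyses use change in the risky driving composite from baseline to post-intervention, which is two time points.
- Analyses (3): a mixed model with three assessment periods (baseline, intervention, 6-month follow-up).

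**The concern.** The sentence is a complete power claim for the outcome headed Primary outcome 1: a sample size, a power, a significance level, a correlation and an effect label. Those parts should fit together for the contrast that the article names as primary. With a correlation of only 0.3, a change score is noisier than a single post-intervention score, so a genuinely small effect would normally need far more than 189 people. The cited prior effects point the other way: they are large and would need far fewer. Neither leads to 189.

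What is at stake is how a null driving result is read. Someone relying on the sentence could conclude that even a small benefit had been looked for with 90% power. If the true power for such an effect is well below that, the trial would be credited with sensitivity it does not have.

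**Working it through.** **Inputs from the article.** N = 189 analysable or 210 recruited; alpha 0.05; "0.3 correlation among the repeated measures", so rho = 0.3; two arms; m = 3 periods in the model, m = 2 for the primary contrast.

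**Assumptions.** 1:1 allocation; two-sided test; 'small' taken as either f = 0.10 (partial eta squared 0.01) or d = 0.20.

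**Step 1: the figure that does reproduce.** 189 / 0.9 = 210. The attrition allowance is correct.

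**Step 2: f = 0.10, group-by-period interaction.** Noncentrality lambda = f² × N × m / (1 − rho), with df (m − 1) and (N − 2)(m − 1).

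| m | lambda at 189 / 210 | power at 189 / 210 | N for 90% |
|---|---|---|---|
| 2 (baseline to post) | 0.01×189×2/0.7 = 5.4 / 6.0 | 64% / 68% | 370 |
| 3 (as modelled) | 0.01×189×3/0.7 = 8.1 / 9.0 | 72% / 77% | 297 |
| 6 (weekly, not described) | 0.01×189×6/0.7 = 16.2 / 18.0 | 89% / 92.5% | 194 |

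A between-group test averaged over three periods has 47% / 51%.

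**Step 3: d = 0.20, two-arm comparison of means.** SE = k × √(4/N), and √(4/189) = 0.1455. Power = Φ(0.20/SE − 1.960).

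- Change score: k = √(2 × 0.7) = 1.183; SE = 0.172; power 21% (23% at 210).
- Baseline-adjusted: k = √(1 − 0.09) = 0.954; SE = 0.139; power 30% (33% at 210).
- Baseline-adjusted mean of both post-baseline periods: k = √(0.65 − 0.09) = 0.748; SE = 0.109; power 45% (49% at 210).
- Post score alone, one-sided: 39% (42% at 210).

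**Step 4: what 189 does deliver.** Difference detectable with 90% power = (1.960 + 1.282) × SE.

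- Change score: 3.242 × 0.172 = 0.56 SD (0.53 at 210).
- Baseline-adjusted: 3.242 × 0.139 = 0.45 SD (0.43 at 210).
- Baseline-adjusted mean of both post-baseline periods: 3.242 × 0.109 = 0.35 SD (0.34 at 210).

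**Step 5: what would give 189.** The three-period interaction has 90% power at N = 189 when f is about 0.125 (f = 0.125 gives N = 191). If the arms differ by d at both post-baseline periods and not at baseline, f = d/√18, so d = 0.125 × 4.243 = 0.53 SD. For two periods f = d/4, so even the f = 0.10 benchmark is a 0.40 SD difference between arms.

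**Step 6: the cited basis.** f = √(η²/(1 − η²)). For 0.12: √(0.12/0.88) = 0.37. For 0.37: √(0.37/0.63) = 0.77. The three-period interaction would need only about 7 to 24 people in total for effects of that size; the between-group test would need about 12 to 44.

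**The case against.** The best defence is that 'small' is never given a number, and that a condensed article may leave the effect size and test to a full protocol. That stands as far as it goes: f = 0.10 and d = 0.20 are benchmarks brought to the text, so the result is that the claim does not reproduce for the design described, not that a known calculation was done wrongly.

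The second argument is that the driving data are aggregated by week and each assessment lasts two weeks, giving six weekly measures. With six measures f = 0.10 gives 89% at 189 and 92.5% at 210, so it would be wrong to call 64 to 72% the most favourable reading possible. But six levels match neither the three periods under Analyses nor the baseline-to-post change under Primary outcome 1. The effect is not small in SD terms either: f = 0.10 there is about 0.42 of a weekly SD, or 0.42/√0.65 = 0.53 SD of a two-week mean.

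Third, on the partial eta squared scale that the article uses, f = 0.125 is about 0.015, nearer the small benchmark (0.01) than the medium one (0.06). This is fair, and it may be how the label arose. It does not rescue the claim, because the same f is about half an SD between arms.

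Two stronger readings are tempting and are not supported. A reader might infer that nothing below half an SD can be detected. The baseline-adjusted contrast reaches 90% at 0.45 SD and has 82% power at 0.40 SD with 189, and averaging both post-baseline periods lowers the 90% point to 0.35 SD. A reader might also infer that the statement on secondary outcomes is false and should go. It rests on a cited source that is not available here, so that is not established.

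Finally, Analyses commits to confidence intervals and magnitude estimates, so a null result would carry its own precision. That limits the harm but does not make the power sentence correct.

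**Conclusion.** The point holds for the power sentence on the primary driving outcome. Against a stated 90%, the power for a conventionally small effect on the baseline-to-post contrast is 64% (189) or 68% (210) at f = 0.10, and about 21 to 30% with 189 at d = 0.20. The three-period interaction at f = 0.10 gives 72% or 77%. With 189 completers, 90% power on the primary contrast corresponds to 0.56 SD for change or 0.45 SD with baseline adjustment. The earlier effects quoted as the basis are large and support neither the label nor the number.

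This rests on 1:1 allocation, a two-sided 5% test, rho = 0.3 as stated, and the usual benchmarks for 'small'. It does not depend on choosing between the two benchmarks. Nor does it show that 210 is the wrong number to recruit: the article gives no smallest difference of interest for driving against which to judge that.

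**What to change.** Keep the target of 210. In the Sample size section, replace 'small' with the numeric detectable difference for the primary driving contrast, for example: with 189 completers, a two-sided 5% test and a correlation of 0.3, the trial has 90% power for a between-group difference of 0.56 SD in baseline-to-post change, or 0.45 SD with baseline adjustment. Name the one that matches the planned analysis. If a weekly or averaged analysis was intended, say so and give the figure for it. The partial eta squared range should not be presented as the source of a small effect.

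The cost is rewording one paragraph and a less favourable stated detectable effect. Recruitment, conduct and the planned model are unchanged.

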#### Participants and recruitment

1.1.3

We will recruit young adult (18–24 years), males and females who currently hold an Australian driver's license (Provisional 1 and 2, or Open/Full). The inclusion and exclusion criteria are presented in Table 1. Inclusion criteria were defined to select participants who may be at increased risk of sleepiness-related crashes, consistent with the AASM sleep duration recommendations. Exclusion criteria were defined to minimise the impact of uncontrollable variables by randomisation (see Table 1).

**Table 1 tbl1:** Study inclusion and exclusion criteria.

*Inclusion* Criteria	*Exclusion* Criteria
• Self-reported sleep of < 7 h s per night • Self-reported sleep of < 6 h s on at least two nights per week. • Regular drivers (driving on > 3 days per week) • Everyday access to a passenger vehicle and a mobile device (smartphone) • Willing to make changes to either a sleep or nutrition related lifestyle behaviour	• Overnight shift worker (i.e., any shifts falling between 12am and 6am) • Travelled across >3 time zones within the past 3 months or intention to travel within the first 3 months of the study • Medically diagnosed clinical sleep or eating disorder. • Use of over-the-counter substances with psychoactive properties (e.g., Ginko Biloba, St. John's Wort) • Use of medically prescribed stimulants, antidepressants, antianxiety, antipsychotic, mood stabilising medications, sleep medications or appetite suppressants • Pregnant or planning a pregnancy in the following 10-month period • Sole carer of a child • Regular smoker – due to increased risk of sleep-related issues and motor vehicle accidents.

Recruitment for the trial will be promoted across metropolitan Brisbane and the Sunshine Coast (Queensland, Australia), using various strategies specifically targeting young adult populations including: in-community flyer distribution around universities, shopping centres, and community noticeboards, as well as targeted social media advertising, through Instagram and Facebook community groups for young adults (e.g. University media and Instagram pages), and snowballing. Participants will be compensated for their time taken to complete the trial, receiving a total of $450 AUD, paid in two instalments; $250 paid upon completion of the intervention laboratory session and $200 paid upon completion of the follow-up laboratory session.

##### Randomisation and blinding

1.1.3.1

Following successful completion of screening and informed consent procedures, participants will be randomly allocated to either the Sleep Intervention group or the Nutrition ‘Placebo’ group by a data manager blind to participant recruitment using a computer-generated randomisation schedule. Participants will not be informed of their group allocation before completion of their baseline laboratory assessments to ensure a stable and equal baseline across participants.

The nature of the intervention does not permit fully blinding participants to their allocation status. Therefore, the trial will be partially blinded to prevent performance and attrition biases. However, the study aims and outcomes will be concealed, and the initial recruitment premise will be '*a study of health, activity, and transport’* to reduce expectancies. Additionally, evaluation of the outcomes will be conducted by staff blinded to participant allocation (e.g., an independent statistician), and the use of objective outcome measures will minimise the risk of ascertainment bias. A full explanation of both the real aims of the research and reasons for the concealment will subsequently be made available to participants upon completion of their participation or upon withdrawal from the study.

##### Trial design and settings

1.1.3.2

This trial employs a randomized, placebo-controlled, parallel groups design (see Fig. 1 for study design schematic). Across an approximate timeline of nine-months, participants will undergo three assessment periods (Baseline, Intervention/Maintenance, Follow-up), three laboratory sessions and a randomised sleep extension (intervention) or nutrition information (placebo control) component. The assessment periods will include naturalistic monitoring of participants’ sleep and driving performance (i.e. when driving their own vehicle in the community). Each assessment period will be followed by a session in the driving simulator laboratory at the study setting.

**Fig. 1 fig1:**
[figure not shown]
Flow diagram of recruitment, allocation, and assessment points at Baseline, Intervention, and Follow-up. Continuous naturalistic measurement refers to measurement undertaken continuously during day-to-day 'life as usual’ activities.

Upon recruitment and following informed consent procedures, participants will complete online pre-baseline questionnaires capturing demographic, health, sleep, risk and driving related information. Participants will then be provided with an actigraph (to be worn on their non-dominant wrist), and an in-vehicle accelerometer. The accelerometer will be installed into the boot/trunk of participants' vehicles. The actigraph will record habitual sleep and the accelerometer will record driving behaviour during a 2-week assessment period. During each assessment period participants will be instructed to continue their lives ‘as per usual’ while completing a daily sleep and/or food craving diary, continuously wearing their actigraph, and driving naturalistically in the community.

The three laboratory sessions (Fig. 1) will follow each of the baseline, maintenance, and follow-up assessment periods. All laboratory sessions will be scheduled within 7–14 days of the end of each data collection period. Participants will be advised to refrain from consuming alcohol on the night before, and any caffeinated beverages at least 4 h before attending the laboratory session. The laboratory sessions include a large array of objective and subjective measures to assess a range of secondary objectives (cognitive and socio-emotional outcomes). The measures used in this session have been carefully selected using validated instruments (i.e. NIH toolbox, PROMIS scales), and physiological assessments (EEG, ECG, eye tracking), alongside driving simulator scenarios developed specifically to elicit data on dimensions of vehicle control.

